#### Safety and adverse event outcomes

An adverse event refers to any medical event related to the use of intervention in human clinical trials, whether or not it is considered intervention-related. All adverse events will be evaluated and recorded on every visit by the clinical research coordinator and physicians.

### Sample size calculation

The primary outcome of our study is the total diuretic doses of the treatment and control groups during hospitalization. In a previous study about the effect of the adenosine A1-receptor antagonist (rolofylline) in acute decompensated HF and renal impairment patients, the mean and standard deviation of total diuretic doses were reported [25]. In the trial, doses of 0, 2.5, 15, 30, and 60 mg of rolofylline were used. Our trial offers conventional treatments to both groups and compares the diuretic doses of the real acupuncture and sham acupuncture groups. Therefore, through consensus of the research team members, we assume the effect of real and sham acupuncture on the diuretics doses will be similar to 15 mg and 30 mg rolofylline, respectively. In the study, the cumulative dose of furosemide usage during hospitalization in the group receiving 30 mg of rolofylline was 223 ± 26 mg. In the group receiving 15 mg, it was reported to be 256 ± 39 mg. In a superiority test, with 80% of power (1-β = 0.8) and 5% of significance level (α = 0.05) in a two-sided *t*-test, calculated sample size of each group was 17 participants. After determining that the dropout rate will be approximately 20%, the sample size of each group was increased to 22; and the total sample size was 44. Sample size was calculated using G-power 3.1 software (Heinrich-Heine-Universität, Düsseldorf, Germany).

### Statistical analysis

The primary outcome of our study is the cumulative amount of diuretic administered to each group. After a normality test, the total amount will be compared by an independent *t*-test (parametric) or a Mann-Whitney U test (non-parametric) according to the normality of the data. If the baseline characteristic is significantly different between the two groups, an analysis of covariance (ANCOVA) will be used to adjust the baseline difference. In baseline characteristics and secondary outcome analysis, binary outcomes will be compared by a chi-square test or Fisher’s exact test. Continuous outcomes will be compared by an independent *t*-test (parametric) or Mann-Whitney U test (non-parametric). MACE will be also be analyzed using the survival analysis method. Statistical analysis will be performed using the R package by a blinded statistician. A 5% significance level will be used. Missing values will be replaced by the last observation carried forward method. If there are more than 20% of drop out participants, sensitivity analysis will be conducted including the data.

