### Outcome measurements: primary endpoint

A detailed outcome measurement schedule is presented in Table 1. The primary outcome of this trial is the cumulative diuretic dose administered from the date of admission to the date of discharge. The total doses of the treatment and control groups will be compared.

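### The primary analysis is chosen by a normality test and a baseline significance test, so no single analysis is fixed in advance and available precision is left to chance

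*Protocol article*

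**What the plan says.** The endpoint is a single continuous quantity. Outcome measurements: primary endpoint states: "The primary outcome of this trial is the cumulative diuretic dose administered from the date of admission to the date of discharge".

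The Statistical analysis section then sets two selectors in sequence.

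- Choice of test: "After a normality test, the total amount will be compared by an independent *t*-test (parametric) or a Mann-Whitney U test (non-parametric"), with the choice made "according to the normality of the data".
- Choice of adjustment: "If the baseline characteristic is significantly different between the two groups, an analysis of covariance (ANCOVA) will be used to adjust the baseline difference".

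No covariate is named. Baseline characteristics are to be tested between groups: "In baseline characteristics and secondary outcome analysis, binary outcomes will be compared by a chi-square test or Fisher’s exact test", with a t-test or Mann-Whitney U test for continuous ones. The only level given is: "A 5% significance level will be used".

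The Sample size calculation section rests on an unadjusted comparison, "with 80% of power (1-β = 0.8) and 5% of significance level (α = 0.05) in a two-sided *t*-test", giving 17 per group and 22 after allowance for dropout.

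**The concern.** In a randomised trial, a significant baseline difference is a chance event. Its probability is the level of the test, and it says nothing about whether the characteristic predicts diuretic dose. A covariate earns its place in the model by predicting the outcome. The stated rule lets chance imbalance decide instead, so a strong predictor is usually left out and a weak one may be put in.

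The normality test adds a second fork. With about 17 to 22 patients per arm it is an unreliable guide, and the two tests it chooses between address different quantities (a difference in means, or an ordering of ranks). The text also leaves one combination open: it does not say what is done when the doses are non-normal and a baseline characteristic also differs.

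Two things are at stake: a primary result whose meaning is known before the data are seen, and the precision that adjustment could add in a trial of 44 patients.

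**Working it through.** **Inputs from the article.** Reference means and SDs: "the cumulative dose of furosemide usage during hospitalization in the group receiving 30 mg of rolofylline was 223 ± 26 mg", and 256 ± 39 mg in the 15 mg group. Two-sided α = 0.05, 80% power, 17 per group before 20% dropout, 1:1 allocation.

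**Assumed, because the article gives no figure.** The correlation ρ between covariate and dose (0.3, 0.5, 0.7). Baseline tests at the 5% level. Shapiro-Wilk in each arm as the normality test. ANCOVA taking over whenever the baseline test is significant.

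**1. The plan's own figure.**
- Difference = 256 − 223 = 33 mg.
- Pooled SD = √((26² + 39²)/2) = 33.14 mg.
- d = 33/33.14 = 0.996.
- Noncentral t: power is 77.8% with 16 per group and 80.4% with 17.
- Dropout: 17/(1 − 0.20) = 21.25, rounded up to 22.

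The stated 17 and 22 are reproduced.

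**2. How often adjustment is triggered.** For k independent characteristics the probability is 1 − 0.95^k.

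| k | any adjustment |
|---|---|
| 1 | 5.0% |
| 2 | 9.8% |
| 5 | 22.6% |
| 10 | 40.1% |
| 15 | 53.7% |

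The simulations below, with one covariate, triggered it in 4.6% to 5.5% of runs.

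**3. What a fixed ANCOVA could give, by formula.** With one covariate the effective standardised difference is d/√(1 − ρ²), on one fewer degree of freedom.

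| ρ | d/√(1 − ρ²) | power, 17 per group | n per group for 80% |
|---|---|---|---|
| none | 0.996 | 80.4% | 17 |
| 0.3 | 1.044 | 83.8% | 16 |
| 0.5 | 1.150 | 90.1% | 13 |
| 0.7 | 1.394 | 97.6% | 10 |

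**4. The rule itself, simulated.** Normal data, 17 per arm, one covariate, 8,000 runs per scenario. Monte Carlo standard error near 80% power is √(0.8 × 0.2/8000), about 0.4 points.

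| ρ | power, stated rule | power, fixed ANCOVA | gain | type I error, stated rule |
|---|---|---|---|---|
| 0.3 | 80.4% | 82.8% | about 2 points | 5.1% |
| 0.5 | 80.7% | 89.2% | about 8 points | 4.4% |
| 0.7 | 82.5% | 97.5% | 15 points | 4.2% |

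The simulated ANCOVA power is slightly below the formula because the formula ignores the small cost of chance imbalance in the covariate.

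**5. The normality gate.** It sent about 10% of truly normal data sets to Mann-Whitney, and 94% of log-normal ones (SD 0.8 on the log scale, assumed; 5,000 runs). In the log-normal case at ρ = 0.5, power was 77.5% under the rule and 74.6% for ANCOVA on the raw scale. A fixed ANCOVA on the wrong scale therefore need not beat the rule. On the log scale those data are the normal case of step 3, where the formula gives 90.1%, but only because the log is the scale on which they were generated.

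**The case against.** The case for leaving the rule alone has several parts.

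- *It is a stated rule, applied by a blinded statistician.* True, and this limits the scope for choosing by result. The form of the primary analysis still depends on the trial data.
- *Covariate names and the normality test belong in a statistical analysis plan.* Their absence is not the point. What the article does state, selection by significance, is poorly chosen and would have to be replaced, not merely elaborated.
- *The trial keeps its planned power.* This stands. A reader might infer that power already secured is thrown away. The sample size was set for an unadjusted t-test and its 80% reproduces, so what is lost is a possible gain.
- *The gain may be small.* This stands too. At ρ = 0.3 it is about 2 points, and cumulative inpatient dose has no baseline value of its own, so 0.7 is not an obvious central case.

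Three other stronger readings are tempting and are not supported. Two-stage selection might be thought to inflate type I error; the simulated values were 4.2% to 5.1% for normal data and 3.8% for log-normal data. Adjustment might be said to be skipped in 95% of trials; that holds per covariate only. The plan might be read as returning to a parametric ANCOVA on doses just declared non-normal; the text does not settle that case, and ANCOVA in any event concerns the residuals, not the raw outcome.

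**Conclusion.** The point holds as a weakness of prespecification and efficiency, not of validity. The article ties the primary analysis to two tests on the trial data, and the baseline test selects covariates by chance: 5% of the time for each, and about 40% to 54% of the time for at least one if 10 to 15 independent characteristics are tested. Characteristics that are correlated with each other would change the latter figures.

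For one covariate, at the article's own effect size and 17 per arm, a prespecified ANCOVA would add about 2 to 15 points of power. That range rests wholly on the assumed correlations of 0.3 to 0.7, on normal data, and on the reading of the rule set out above. With skewed doses, the gain also depends on choosing a suitable scale. The sponsor should make the change, although the planned comparison is not invalid without it.

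**What to change.** Before unblinding, replace the two selectors with one named primary analysis:

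- ANCOVA of log total diuretic dose on treatment group, with the effect reported as a ratio of geometric means and its 95% confidence interval. The log scale is proposed because cumulative doses are likely to be right-skewed. This is an assumption: the reference SDs are only 12% (26/223) and 15% (39/256) of their means. If the trial's doses are that tight, the log and raw scales will give nearly the same test, so little is lost. Say in advance how a zero dose would be handled.
- One or two covariates fixed beforehand and used whatever the observed imbalance, for example log NT-pro BNP and creatinine. Table 1 of the article schedules NT-pro BNP and the routine blood test, which includes creatinine, at screening.
- No normality or baseline significance test as a selector. Keep the unadjusted t-test and the Mann-Whitney U test as sensitivity analyses.

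Diuretic dose before randomisation should not be added as a covariate without further definition. Table 1 shows only a check of concomitant medication, and the endpoint already counts dose from admission.

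The cost is a change of wording in the analysis section, one or two degrees of freedom, and an effect expressed as a ratio instead of a difference in milligrams. No new data, visits or patients are needed.

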### Intervention

#### Study flow

If the participants voluntarily sign informed consent during admission to the cardiology ward, participants will be screened according to inclusion and exclusion criteria on the screening day. After the subject fulfills the criteria, the basic characteristics and prognostic factors of each participant will be evaluated. The subjects will be randomized into an intervention and a control group with a 1:1 allocation ratio on the same day; the screening day and Day 1 will usually be the same day. From Day 1 to Day 5, the participants will receive electroacupuncture treatment or sham electroacupuncture treatment once a day for consecutive 5 days according to their allocated group. After discharge, participants will visit KHMC three times. Visit (V1) will be 7 days after discharge. Visit 2 (V2) will be 28 days after discharge. Visit 3 (V3) will be 180 days after discharge. On the day discharge (Day 5) and V2, blood tests, quality of life (QOL), and a pattern identification questionnaire according to traditional East Asian medicine (TEAM) theory will be evaluated. On V3, cardiac function and MACE will be evaluated by echocardiography (Table 1). Participants will be withdrawn from the study if they 1) re-admit to hospital related to cardiac or kidney dysfunction 2) withdraw of consent by participants 3) worsening cardiac function 4) the principle investigator judged that participants can not continue the research.

**Table 1 Tab1:** Study schedule

Study period	Screening visit	Acupuncture treatment period					Follow-up period		
Visit	Screening	D1	D2	D3	D4	D5	V1	V2	V3
Informed consent	X								
Demographics and history collection	X								
Inclusion and exclusion criteria	X								
Randomization		X							
Physical examination and vital signs check	X	X	X	X	X	X	X	X	X
Body weight	X	X	X	X	X	X	X	X	X
Symptoms check (NYHA Functional Class)	X	X	X	X	X	X	X	X	X
Adverse events	X	X	X	X	X	X	X	X	X
Concomitant medication check	X	X	X	X	X	X	X	X	X
Routine blood test^a^	X		X			X		X	X
NT-pro BNP, hs-CRP	X					X		X	
Cardiac biomarkers^b^		X				X			
Cardiac function (echocardiography)	X								X
Electrocardiogram and HRV		X				X			
QOL and symptom questionnaire^c^		X						X	
Credibility and AES		X				X			
Blinding test		X				X			
Acupuncture treatment		X	X	X	X	X			

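### Blanket LOCF scores a missing follow-up as zero change in outcomes measured twice, leaves the primary total undefined after early withdrawal, and is checked only above 20% dropout

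*Protocol article*

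**What the plan says.** The Statistical analysis section gives one rule for incomplete data, "Missing values will be replaced by the last observation carried forward method", and one condition for checking it: "If there are more than 20% of drop out participants, sensitivity analysis will be conducted including the data".

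Four other places bear on how the rule works:

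- The primary outcome is the "cumulative diuretic dose administered from the date of admission to the date of discharge", compared between arms.
- Study flow lists the grounds for withdrawal. They include cardiac or renal re-admission, withdrawn consent, and "3) worsening cardiac function 4) the principle investigator judged that participants can not continue the research".
- Table 1 schedules echocardiography at screening and V3, the QOL and symptom questionnaires at D1 and V2, and cardiac biomarkers and HRV at D1 and D5. The sections on these outcomes compare change from baseline.
- The sample size section allows for about 20% dropout, taking 17 per group to 22.

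**The concern.** LOCF assumes that a patient's state stays where it was last seen. Here the withdrawal criteria select patients for whom that is unlikely: someone taken out for "3) worsening cardiac function" who then lacks the V3 echocardiogram would be recorded as having had no change in cardiac function. Where baseline is the only earlier value, the imputed change is zero whatever happened, and the analysis counts it as an observation.

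The primary outcome is an accumulating quantity, and the article does not say what is carried forward for a patient who leaves before discharge. Carrying the running total forward adds no further diuretic, so the total is too low, which is the favourable direction. Carrying the last daily dose forward assumes no tapering and may overstate the total.

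The only planned check is switched on above roughly the dropout rate that the trial expects. Its wording about including the data also leaves open whether dropouts are in the main analysis at all.

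**Working it through.** **The plan's own figure.** Inputs from the Sample size calculation section: "group receiving 30 mg of rolofylline was 223 ± 26 mg"; for 15 mg, "it was reported to be 256 ± 39 mg"; "with 80% of power (1-β = 0.8) and 5% of significance level (α = 0.05) in a two-sided" t-test.

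- Difference: 256 − 223 = 33 mg. SD = √((26² + 39²)/2) = 33.14 mg. Standardised difference = 33/33.14 = 0.996.
- Power from the noncentral t distribution is 77.8% at 16 per group and 80.4% at 17, so 17 is reproduced. 17/0.8 = 21.25, rounded up to 22, is also reproduced.
- With complete totals for all 22 per arm, power is 89.7%.

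**Outcomes measured twice.** If k of n follow-ups are missing and the observed mean change is m, the LOCF mean change is m(n − k)/n.

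- k = 2 of 22: 20/22 = 91% of m
- k = 4 of 22: 18/22 = 82%
- k = 5 of 22: 17/22 = 77%

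A group difference shrinks by the same factor if dropout is equal in the two arms and dropouts would have changed as completers did. With unequal dropout, for example 6 and 2 of 22, and the same true change m in both arms, the LOCF means are 16m/22 and 20m/22. That is a spurious difference of 4m/22 = 0.18m.

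The zeros also enter the standard error. With p = 4/22, the LOCF variance of the mean is about (1 − p)(s² + p·m²)/n, against s²/(n(1 − p)) from the 18 observed patients. LOCF gives the smaller value when (m/s)² < (1/(1 − p)² − 1)/p = (1.494 − 1)/0.1818 = 2.72, that is, when the mean change is below about 1.65 SD.

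NT-pro BNP and hs-CRP are different: Table 1 gives them a D5 value, so a missing V2 takes that value and not the baseline. Study flow also mentions QOL and the pattern questionnaire on the day of discharge, whereas Table 1 and the pattern identification section give D1 and V2. If a D5 questionnaire exists, it would be the value carried.

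**Primary outcome, illustration only.** Assumptions: a common mean of (223 + 256)/2 = 239.5 mg, spread evenly over 5 days (47.9 mg/day), with LOCF acting on the running total. None of these is stated in the article. Shift in an arm's mean = uncounted dose × extra withdrawals/22.

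| Withdrawn after | Uncounted dose | 2 extra of 22 | 4 extra of 22 |
|---|---|---|---|
| Day 4 | 47.9 mg | 4.4 mg | 8.7 mg |
| Day 3 | 95.8 mg | 8.7 mg | 17.4 mg |
| Day 2 | 143.7 mg | 13.1 mg | 26.1 mg |
| Day 1 | 191.6 mg | 17.4 mg | 34.8 mg |

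The Day 3 row is 26% and 53% of the planned 33 mg.

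Simulation on the same assumptions (40,000 runs, 22 per arm, t-test):

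- No true effect, 6 versus 2 withdrawals: type I error of 8% to 11% across the four rows.
- Planned effect, 4 withdrawals in each arm: power of 83%, 53%, 14% and 1% for Days 4, 3, 2 and 1.

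These rates are for the t-test. The plan switches to the Mann-Whitney test if normality fails, and they do not carry over to that test.

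**The trigger.** 20% of 44 is 8.8. Eight dropouts (18.2%) bring no sensitivity analysis; nine (20.5%) do.

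**The case against.** A reader might infer that the plan scores all diuretic after dropout as zero and so favours the arm with more withdrawals. The article does not support that as fact. It does not say whether LOCF acts on the running total or on daily doses, and the second could reverse the direction. Only withdrawal before discharge matters here: D5 is the discharge date, re-admission can only come later, and a later dropout leaves the primary total complete. The 20% allowance is not said to be in-hospital, so eight losses out of 44 cannot be treated as eight threatened primary values. The milligram figures borrow totals from another drug's trial and assume flat dosing over five days. No passage suggests unequal in-hospital withdrawal.

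A reader might also infer that the plan both fills dropouts by LOCF and excludes them. Both cannot hold. If dropouts are excluded, LOCF never touches their totals and the illustration lapses. The wording is ambiguous, but a contradiction is not established.

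On the trigger, using the full allowance of 5 per arm gives 10/44 = 22.7%, which would bring in the sensitivity analysis. MACE needs no change, since survival analysis is already planned for it.

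All of this stands, and it makes the primary-outcome part conditional. It does not touch the zero change in outcomes measured twice, which follows from the stated rule and Table 1 alone.

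**Conclusion.** The concern holds for the outcomes with a single follow-up. The stated rule gives them a change of exactly 0 when that follow-up is missing, including for patients withdrawn because they got worse. At 4 of 22 missing per arm, the attenuation is to 82%, given equal dropout and dropouts who would have changed like completers. For the questionnaires it also assumes the Table 1 schedule.

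For the primary outcome, the defect is that the rule is undefined for an accumulating total. The bias could go either way and arises only on withdrawal before discharge. The 8.7 to 17.4 mg shift shows what the running-total reading could do under the stated assumptions; it is not an estimate of the bias in this trial.

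The sensitivity threshold is badly placed because dropout close to the expected rate can pass unchecked. The place of dropouts in the main analysis needs a plain statement.

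**What to change.** Amend the Statistical analysis section as follows:

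1. State that all randomised participants are analysed in the arm to which they were allocated.
2. Take the in-hospital diuretic total up to discharge from the chart for every participant who has not withdrawn consent to data collection, including those who stop study treatment. The primary outcome then needs little or no imputation.
3. Replace LOCF with multiple imputation or a mixed model for the change-from-baseline outcomes.
4. Run a sensitivity analysis under unfavourable assumptions for dropouts, whatever the dropout rate.

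The cost is slightly more analysis work and somewhat wider intervals. Item 2 uses records that the ward already keeps, but consent must cover continued data collection. Because recruitment has begun, the change should go through the amendment route that the article describes.

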### Quality control

Acupuncture treatment sessions will be conducted by KMDs who have at least 2 years of clinical experience and more than 8 years of education in acupuncture and meridian. SOPs will be provided to practitioners to ensure identical treatment procedures. The SOPs will contain the treatment regimen and process. A moderate grade of doctor-patient relationship is allowed. The doctor is allowed to answer the questions of participants except those concerning the treatment group assignment. Researcher meetings will be held regularly to ensure the quality of the clinical trial. Assessor will be educated about evaluation and data collection according to SOPs. Study process will be monitored by human research protections program.

### Data management

Data will be entered by independent researcher. Data will be stored on password-protected computers. Data manager who is independent from competing interests can only access to the data.

### Ethics approval and registration

This study was planned in compliance with the Korean Good Practice Guidelines and the Helsinki Declaration to protect the rights of participants. This study was approved by the Institutional Review Board of Kyung Hee Medical Center (KMC IRB 1601–01-A1). An initial version of this protocol was approved by KMCIRB on March 23, 2016. Written informed consent will be obtained from all participants. The participants will be informed about the risks, benefits, responsibilities, alternatives, and rights during the study. This study has been registered with the Clinical Research Information Service (CRIS), Republic of Korea, KCT0002249 (registered February 14, 2017). If protocol is modified, it will be reported to IRB and announced to the participants and investigators. Personal information will be collected by clinical research coordinators and stored password-protected computer to protect confidentiality.

